### Participants

2.2

Participants are domestic or international undergraduate, graduate or PhD students enrolled in the seven universities mentioned above. They will be eligible if they (i) are aged 16 or older, (ii) are enrolled at one of the participating universities, (iii) have access to a computer, laptop, tablet or mobile device with internet access (iv) score 32 or above on the Irrational Procrastination Scale (IPS) and (v) provide informed consent. We used the cut-off score of 32 as a previous study successfully used it to identify individuals suffering from procrastination (Rozental et al., 2015b). Participants are excluded if they show any suicidal risk by identifying if they have had thoughts of killing themselves or have made plans of killing themselves in the past year and then responding to the question “How likely do you think it is that you will act on this plan in the next 12 months?” with: somewhat likely, likely or very likely. Recruitment started on 19th November 2021.

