#### Primary outcome – procrastination tendencies

2.7.1

*The Irrational Procrastination Scale* (IPS) is used to assess procrastination tendencies by assessing the extent to which participants procrastinate (Steel, 2007, Steel, 2010). This scale contains nine items scored on a five-point Likert scale ranging from 1 (very seldom or not true to me) to 5 (very often true or true to me). An example of an item is “My life would be better if I did some activities or tasks earlier”. The total scores can range from 9 to 45, with a higher score indicating higher levels of procrastination. With a good internal consistency of α = 0.91 (Steel, 2010), test-retest reliability of *r* = 0.84 (Guilera et al., 2018; Rozental et al., 2014), the IPS has also shown good content, structural, and substantive validity (Shaw and Zhang, 2021).

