### Sample size estimation

2.8

The power calculation is based on head-to-head comparison of the guided web-based intervention versus the waiting list (*t*-test). We anticipate a conservative estimate of Cohen's d = 0.50 based on a recent meta-analysis of randomized controlled trials that indicated an effect size of 0.55 for cognitive behavioral treatments for procrastination (Rozental et al., 2018b). Thus, if we set the statistical power at 0.8 and alpha at 0.05, according to two tails hypothesis, we need 63 participants per group (total *n* = 126) to detect an effect size of Cohen's d = 0.50. Previous literature has shown that guided web-based interventions have a dropout rate of 28 % (Richards and Richardson, 2012). Thus, considering the potential dropouts, the minimum required sample for the RCT is 176 participants with a target of 88 participants in each arm.

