#### Primary outcome

2.9.1

Change in procrastination scores on the IPS will be assessed at post-treatment and follow-up assessments using multilevel mixed models linear regression with a restricted maximum likelihood algorithm for normally distributed data. Binomial models will be used for skewed data. The post-treatment score will be used as the dependent variable and trial arm condition (web-based transdiagnostic intervention vs WL) as independent while adjusting for baseline IPS scores. We will calculate the effect size of Cohen's d by subtracting the intervention group's average score on IPS measures from the average scores of the control group at the post- treatment and dividing the results by the pooled standard deviations. In addition, we will calculate the means and standard deviations of the groups at all time points. Analogously, the Cohen's d will be calculated for the difference score between the post-test measurement (t3 for the intervention group and t4 for the wait list group) and follow-up assessment (6 months, t5).

The reliability change index (RCI) will determine clinically significant change (Jacobson and Truax, 1991). The RCI will be calculated using the standard deviations at baseline and the test-retest reliability coefficient of the IPS (Guilera et al., 2018; Rozental et al., 2014). Participants will be classified as improved, deteriorated or no change based on the RCI for pretest and posttest measures.

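### The reliable change index alone is labelled clinically significant change, so a student can be counted as a clinically significant improver while still scoring at or above the trial's own entry cut-off of IPS 32

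*Protocol article*

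**What the plan says.** Section 2.9.1 (Primary outcome, under Data analyses) states: "The reliability change index (RCI) will determine clinically significant change". It gives the ingredients, "The RCI will be calculated using the standard deviations at baseline and the test-retest reliability coefficient of the IPS", and the resulting categories: "Participants will be classified as improved, deteriorated or no change based on the RCI for pretest and posttest measures". Neither this section nor any other part of the article sets a condition on the post-test score itself.

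The only IPS threshold in the article is the entry criterion of 32 or above (section 2.2), which is used again for invitations after the survey (section 2.3). Section 2.2 gives that threshold a meaning: "We used the cut-off score of 32 as a previous study successfully used it to identify individuals suffering from procrastination".

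Section 2.7.1 describes the scale. "The total scores can range from 9 to 45, with a higher score indicating higher levels of procrastination", and the reliability is given as "test-retest reliability of *r* = 0.84". Table 1 places the IPS at T0 (screening, which serves as the pretest), at T2 for the intervention group and at T3 for the waitlist group, both four weeks after baseline.

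**The concern.** A reliable change index divides a difference score by its standard error of measurement. It can support the statement that a change is unlikely to be noise. It cannot support a statement about clinical status, because neither the baseline SD nor the reliability carries information about the level reached. Section 2.9.1 nevertheless makes it the sole determinant of clinically significant change.

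This conflicts with the protocol's own use of 32. The same student can be a clinically significant improver under section 2.9.1 and, under section 2.2, still score in the range taken to identify people who suffer from procrastination. That student would again meet the IPS entry criterion.

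This is the only responder classification specified for the primary outcome, and readers are likely to take a percentage labelled clinically significant as the trial's clinical result. As written, that percentage pools students who left the problem range with students who did not.

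**Working it through.** The article states no RCI threshold, IPS standard deviation or responder rate, so there is no figure of its own to reproduce on this point.

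**Inputs from the article**
- Test-retest reliability r = 0.84 (section 2.7.1).
- IPS range 9 to 45, higher is worse (section 2.7.1).
- Entry at 32 or above (section 2.2), so pretest scores lie in 32 to 45, which is 14 possible values.

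**Assumptions**
- Critical value 1.96, because the article gives none.
- Baseline SD, varied over what is possible. For scores confined to 32 to 45 the SD cannot exceed half the range, (45 − 32)/2 = 6.5 (6.52 with the n − 1 divisor at n = 176).

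**Threshold**
- Standard error of measurement = SD × √(1 − 0.84) = 0.4 × SD.
- Standard error of a difference = √2 × 0.4 × SD = 0.566 × SD.
- Smallest reliable change = 1.96 × 0.566 × SD = 1.109 × SD.

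**Who can be improved and still at 32 or above**

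| Baseline SD | Threshold | Smallest whole-point fall | Entry scores that allow it | Example |
|---|---|---|---|---|
| 3 | 3.33 | 4 | 36–45 (10 of 14) | 45 → 41 |
| 3.5 | 3.88 | 4 | 36–45 (10 of 14) | 45 → 41 |
| 4 | 4.43 | 5 | 37–45 (9 of 14) | 40 → 35 |
| 5 | 5.54 | 6 | 38–45 (8 of 14) | 45 → 39 |
| 6.5 (maximum) | 7.21 | 8 | 40–45 (6 of 14) | 45 → 37 |

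The overlap exists at every SD compatible with the entry rule. The choice of 1.96 is not critical either. A critical value of 1.645 widens the overlap (at SD 6.5 the threshold is 6.05, a 7-point fall, entry scores 39–45). To remove it altogether at SD 6.5, the threshold would have to exceed 45 − 32 = 13 points, that is, a critical value above 13/(0.566 × 6.5) ≈ 3.5.

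The last columns count score values, not students. Scores cut off at 32 tend to cluster near 32, so the proportion of students affected needs a distribution.

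**Illustrative size**

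Simulation, 2 million draws per scenario: untruncated IPS mean 30, 32 or 34 and SD 5 or 6; error variance set by r = 0.84; entry at an observed score of 32 or above; true mean fall 2 or 4 points with SD 3; scores rounded and bounded to 9–45. Share of those classed as improved who still score 32 or above:
- with the SD of the truncated (enrolled) sample, as section 2.9.1 implies: 16% to 38%;
- with the untruncated SD: 9% to 27%.

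The lowest values come from mean 30, SD 5, fall 4; the highest from mean 34, SD 5, fall 2. With the truncated SD, the affected group is about 9% to 19% of all enrolled students.

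A second set of assumptions (mean 36 to 39 before truncation, SD 4 to 5, mean fall 2 to 6, SD of change 5) gave about 25% to 55% of improvers.

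**The case against.** Several points on the other side have force.

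- **The categories are neutral.** Improved, deteriorated and no change are what an RCI can deliver, and a student who goes from 45 to 41 at SD 3.5 has improved reliably. No recovered or remitted category is claimed. This stands, and it locates the fault: the label clinically significant, not the classification.
- **It does not concern every student still at 32 or above.** A reader might infer that anyone who remains in the entry range is counted as improved. That is not so. The fall must reach the threshold, so at SD 3.5 a student who enters at 32 to 35 cannot be misdescribed in this way. In every simulated scenario with the trial's own SD under the first set of assumptions, most improvers (62% to 84%) did leave the range.
- **Bias in the treatment effect.** A reader might infer that the comparison between arms is distorted. Nothing in the article supports this. The same rule applies to both arms, no test or decision is tied to the classification, and the primary analysis is a mixed model on the continuous IPS score.
- **What the cited method requires.** It is tempting to argue that the methods paper cited for the RCI itself demands an end-state criterion. That paper is not at hand, and the point does not need it: the conflict is between sections 2.9.1 and 2.2 of the article.
- **The cut-off of 32 is an entry rule, not a recovery threshold.** This is correct; the article does not call it a boundary of normal functioning. It is, however, the only IPS level to which the article gives a clinical meaning.
- **The article is condensed.** An analysis plan could add a further responder definition. But the sentence in section 2.9.1 is a stated rule with a wrong label, not an omitted detail.

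**Conclusion.** The point holds as a problem of labelling and interpretation. Section 2.9.1 calls clinically significant a result that shows only change beyond measurement error, and at every baseline SD possible on 32 to 45 some students can receive that label while still at or above 32. That existence result rests on r = 0.84 from the article and on the assumed 1.96, to which it is not sensitive.

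The size is less certain. The ranges of 16% to 38% and 9% to 27% of improvers, and the 25% to 55% under other assumptions, depend on IPS distributions that the article does not give; they illustrate that the share need not be negligible and are not predictions. The primary analysis, the effect-size estimates and the sample size of 176 are untouched. The matter should be settled before results are seen, because it governs what the trial can say about clinical benefit and because a responder definition chosen afterwards would be post hoc.

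**What to change.** In section 2.9.1:

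1. Rename the RCI categories reliable improvement, no reliable change and reliable deterioration, and do not describe the RCI result alone as clinically significant.
2. Report alongside it, by arm at T2 (intervention) and T3 (waitlist) as defined in Table 1, the proportion with reliable improvement and a post-test IPS below the trial's own cut-off of 32. If the term clinically significant improvement is kept, reserve it for this combined criterion.
3. State the critical value used for the RCI.

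The first step alone removes the contradiction. The second lets readers see how many improvers left the entry range, and reporting both proportions keeps large falls that end above 32 visible.

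Cost: a change of wording and one more variable derived from IPS data already collected. The reported rate of clinically significant response will be lower than under the present label.

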### Assessments and outcomes

2.7

All assessments take place via the Caring Universities platform. At each time point, the participants receive a link to the assessment questionnaire via email. They get reminder emails to fill out the questionnaire 1 and 2 weeks after receiving the questionnaire. If they still don't fill it out, they will be called within a few days to remind them about the questionnaire. The reminder calls are made by the e-coaches, except for the anonymous participants who will be called by a researcher in the study. All outcomes and their time point measures are listed in Table 1.

**Table 1 t0005:** Time point measures of outcome assessments.

Outcome	Measure	Time of assessment					
		T0	T1	T2	T3	T4	T5
Socio-demographics	SR	X					
Procrastination	IPS	X		X	X	X	X
Depressive symptoms	PHQ-9		X	X	X	X	X
Stress	PSS		X	X	X	X	X
Anxiety	GAD-7		X	X	X	X	X
Quality of life	MHQoL		X	X	X	X	X
Satisfaction with treatment	CSQ-8			X		X	
Program usability	SUS-10			X		X	
Satisfaction with e-coach	WAI-I			X		X	
Treatment adherence	Number of modules completed		X	X	X	X	

Note: Abbreviations (alphabetical): CSQ-8: Client Satisfaction Questionnaire – 8 item version; GAD-7: Generalized Anxiety Disorder scale – 7 item version; IPS: Irrational Procrastination Scale; MHQoL: Mental Health Quality of Life questionnaire; PHQ-9: Patient health Questionnaire – 9 item version; PSS: Perceived Stress Scale; SR – self report measure; SUS-10: System Usability Scale – 10 item version; T0: eligibility screening – both groups; T1: baseline screening – both groups; T2: 4 weeks post baseline – intervention group; T3: 4 weeks post baseline – waitlist group; T4: 8 weeks post baseline – waitlist group; T5: 6 months post baseline – both groups; WAI—I: Working Alliance Inventory for guided internet interventions.

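### The IPS reliable change threshold pairs an SD restricted by the entry rule with a reliability from other studies, is applied to the selection score, and is labelled clinically significant change

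*Protocol article*

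**What the plan says.** Section 2.9.1 plans a responder classification beside the primary model. On its meaning: "The reliability change index (RCI) will determine clinically significant change". On its inputs: "The RCI will be calculated using the standard deviations at baseline and the test-retest reliability coefficient of the IPS". On its use: "Participants will be classified as improved, deteriorated or no change based on the RCI for pretest and posttest measures". No end-state criterion is added.

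Three other places determine how the index will behave:
- Section 2.2: to enter, students must "score 32 or above on the Irrational Procrastination Scale (IPS").
- Section 2.7.1: "The total scores can range from 9 to 45, with a higher score indicating higher levels of procrastination". The same section gives the test-retest reliability as r = 0.84 with two citations. It does not say whether those samples were screened for high procrastination.
- Section 2.7, Table 1: the IPS is marked at T0 and blank at T1, and the note defines these as "T0: eligibility screening – both groups; T1: baseline screening – both groups". The only IPS before treatment is therefore the score that admitted the student.

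**The concern.** The index judges a change against measurement error, estimated as SD × √(1 − r). That estimate is valid only if SD and r describe the same population. Selecting students at 32 or above narrows the spread of scores but does not make the questionnaire more precise. A narrowed SD combined with an r from a wider population understates the error and sets the bar for 'improved' and 'deteriorated' too low.

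Using the selection score as pretest adds regression to the mean, which shifts misclassification towards 'improved'.

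The label is a separate matter and needs no assumption. Exceeding measurement error shows that a change is reliable. It does not show that the student has reached a clinically meaningful state.

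At stake are the reported percentages improved and deteriorated in each arm, and how readers will understand them.

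**Working it through.** **What the plan gives.** It states no IPS SD, no threshold and no misclassification rate, so there is no figure of this kind to reproduce. The arm size used below follows from section 2.8: 63 / (1 − 0.28) = 87.5, so 88 per arm.

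**Threshold.** Assuming the conventional 1.96 criterion, which the article does not state:

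threshold = 1.96 × √2 × SD × √(1 − 0.84) = 1.109 × SD.

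Admitted scores lie in 32 to 45. Even if spread evenly over those 14 values, their SD would be 4.03 and the threshold 4.5 points.

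**One case by hand.** Assume an unselected population with SD 6 and r = 0.84.
- True measurement error: 6 × √0.16 = 2.40 points. Matching threshold: 1.109 × 6 = 6.65.
- With a source mean of 30, the SD among those at 32 or above is 3.25 (simulated). Implied error: 3.25 × √0.16 = 1.30. Planned threshold: 1.109 × 3.25 = 3.60.
- On whole-number scores, a drop of 4 points counts as improved, where the matched threshold needs 7.

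**Simulation with no true change.** True score plus two independent errors, rounded and capped at 9 to 45, entry on a first score of at least 32, and that score used as pretest. The source mean and SD are assumptions. Here 0.84 is read as an unselected-population value.

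| Source mean, SD | SD at IPS ≥32 | Planned threshold | Improved | Deteriorated | Improved if the unselected SD is used |
|---|---|---|---|---|---|
| 26, 5 | 2.15 | 2.4 | 33.3% | 8.2% | 6.3% |
| 28, 7 | 3.44 | 3.8 | 27.8% | 10.2% | 5.2% |
| 30, 6 | 3.25 | 3.6 | 21.6% | 8.7% | 4.5% |
| 32, 6 | 3.53 | 3.9 | 19.6% | 9.6% | 3.9% |
| 36, 7 | 4.21 | 4.7 | 13.0% | 7.8% | 2.9% |
| 36, 5 | 3.66 | 4.1 | 6.1% | 4.0% | 2.8% |

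Over means 26 to 36 and SDs 5 to 7 the range is about 6 to 33% improved and 4 to 10% deteriorated. One case (mean 26, SD 6) has its threshold almost exactly at 3 points. It flips between 26% and 37% improved, and between 7% and 12% deteriorated, according to which side of 3 the sample SD falls.

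**Where the excess comes from.** Using the unselected SD, with the selection score still as pretest, brings false improvement to about 3 to 6%. The mismatched SD is therefore the main cause. Regression to the mean (an average drop of 0.3 to 1.5 points over the grid) explains most of what remains.

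**Favourable reading.** Suppose instead that 0.84 holds among students at 32 or above (source means 28, 32 and 36, SDs 5 to 8). False improvement is then 2.3 to 7.1% and false deterioration 1.5 to 3.7%. This requires an unselected reliability of 0.90 to 0.96.

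**Per arm of 88.** Nominal: 88 × 0.025 = 2.2 students. Unselected reading: 88 × 0.061 = 5 to 88 × 0.333 = 29. Favourable reading: 88 × 0.023 = 2 to 88 × 0.071 = 6.

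**The case against.** The strongest reply is that the article does not say where 0.84 was obtained. If the samples were as restricted as this one, SD and r roughly match and little inflation remains. This stands: a reader might infer that many unchanged students will certainly be called improved, and the documents do not establish that. Section 2.7.1 presents 0.84 as a general property of the scale, which leans towards the unfavourable reading but does not settle it.

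The source distribution is also unknown. Section 2.3 recruits partly through advertising and staff recommendation, which may bring in students who already score high. At a source mean of 36 false improvement is 6 to 13%, not 20 to 30%. This stands too, and is why the range is wide.

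A reader might further infer that the trial's main comparison is compromised. It is not. The primary model adjusts for baseline IPS and does not use the index. Both arms share the entry rule, pretest, SD and r, so with no treatment effect they are misclassified alike.

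Finally, the pretest point rests on one blank cell in Table 1, which could be a misprint. It is the smaller part of the problem, and neither the SD mismatch nor the label depends on it.

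**Conclusion.** The point holds in a conditional form. The article pairs a selection-restricted SD with an external reliability, and nothing in it shows that the two belong together. If 0.84 is an unselected-population value, false improvement was above the nominal 2.5% in every scenario tried: about 6 to 33%, with 4 to 10% false deterioration. If 0.84 holds at IPS ≥32, false improvement is about 2 to 7%. Both ranges rest on the assumed source means and SDs, normal true scores and errors, and the 1.96 criterion.

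The label is wrong under either reading, because the index alone shows reliable change and not clinically significant change.

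The harm is confined to the absolute improved and deteriorated rates and their clinical interpretation. It matters most for within-arm reporting, since section 3 says the six-month follow-up allows only within-group comparison and so offers no waitlist rate to set against regression to the mean.

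**What to change.** Before analysis, amend section 2.9.1 as follows:
1. Take SD and r from the same sample and name it. If 0.84 is an unselected value, match it with the SD of the validation sample that produced it, or with the SD of unfiltered IPS scores from the yearly survey if the trial team can obtain them. If it came from a sample restricted like this one, say so.
2. Call the classification reliable change.
3. Reserve the term clinically significant for reliable improvement plus a stated end-state criterion, for example a post-test IPS below the trial's own cut-off of 32. This adds little for lower starters: with a required drop of 7 points, anyone entering at 32 to 38 meets it automatically (38 − 7 = 31), so it binds only from 39 upward.
4. Report each arm's improved and deteriorated rates beside the waitlist rate, and state that they include regression to the mean because the pretest is the selection score.

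The pretest occasion should stay as it is. Recruitment began in November 2021, and adding the IPS at T1 now would give participants different pretest occasions within one trial.

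The cost is one changed input, one renamed outcome and one added definition, with no new data from participants. The downside is a lower reported responder rate.

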#### Secondary outcomes

2.9.2

For quality of life (MHQoL), depressive symptoms (PHQ-9), symptoms of anxiety (GAD-7) and stress-related symptoms (PSS-10), we will follow the same statistical approach described above for the IPS (with means, standard deviations and Cohen's d). Effects of the intervention on depression and anxiety will be analyzed separately for students scoring above the PHQ-9 (10 or more points) and GAD-7 (10 or more points) at baseline.

#### Exploratory analyses – covariates and moderators

2.9.3

Descriptive statistics will be used to describe the socio-demographic characteristics of the participants in terms of age, gender, ethnicity, marital status, and whether the participant is currently receiving any psychotherapy or medication. Descriptive statistics will also be used for data exploration on the outcomes of the CSQ-8, SUS, WAI-I and adherence. Additionally, these outcomes will be tested as predictors and moderators or treatment outcome. The moderation analyses will be conducted using PROCESS macro for SPSS version 3.4. The macro provides bias-corrected 95 % confidence intervals (CI) for the indices using a bootstrap calculation based on 5000 samples (Hayes, 2017).

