Another important potential barrier to effectively treating procrastination is treatment adherence. Rozental et al. (2015a) found that many individuals who receive treatment for procrastination struggle to adhere to and keep up with treatment. Guided treatments have previously been shown to result in better treatment outcomes (Cuijpers et al., 2019). However, unguided treatments are more scalable and affordable (Fairburn and Patel, 2017; Karyotaki et al., 2017). One possible solution is guidance by non-clinicians, which has the promise to be equally effective compared to clinician guidance (Leung et al., 2022). Clinical psychology students, in particular, have successfully supported face-to-face interventions for academic procrastination (Wang et al., 2017). Our study employs trained clinical psychology students as e-coaches to guide the treatment. Should this be an effective form of guidance, it overcomes existing barriers of limited resources in the form of limited available psychologists and counsellors (Watkins et al., 2012). Additionally, it makes treatment more affordable as psychology students offer e-health guidance for significantly lower costs compared to licensed specialists.

Therefore, the present study aims to evaluate the effectiveness of a guided internet-based intervention for procrastination (*GetStarted*) in university students in the Netherlands. Furthermore, since procrastination is associated with various other psychological outcomes (Sirois, 2007; Flett et al., 2016; Stead et al., 2010; Beutel et al., 2016), we will evaluate the effect of this treatment on secondary outcomes such as depression, anxiety, stress, and quality of life. Finally, we aim to gather evidence for potential moderators to treatment effectiveness. These will be socio-demographic characteristics of the participants, satisfaction with treatment and e-coach, system usability and treatment adherence. This will be done to identify target groups that could benefit most from treatment. The main research question is whether *GetStarted* is effective in reducing problematic procrastinating behaviors in university students compared to a waitlist control. The secondary research questions include: What are the effects of *GetStarted* on secondary outcomes of depression, anxiety, stress, and quality of life? Moreover, are there any moderators of treatment effectiveness?

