## Discussion

3

To the best of our knowledge, this is the first randomized controlled trial to examine the effectiveness of an internet-based intervention guided by trained clinical psychology student e-coaches for procrastination in a student population. In addition, this study will examine whether the treatment has any effect on secondary outcomes such as depression, anxiety, stress, and quality of life. We anticipate that the program will be effective in reducing procrastination behaviors. We also expect improvement in depressive symptoms, anxiety, stress and quality of life as they are closely associated with procrastination (Sirois, 2007; Flett et al., 2016; Stead et al., 2010; Beutel et al., 2016).

The results from this high-quality and adequately powered trial will add to the scarce evidence on the effectiveness of a guided internet-based intervention for treating procrastination in university students. We believe this study could provide a flexible and low-intensity treatment for procrastination and prevent common mental health problems in students. A recent meta-analysis on e-health interventions showed that guidance by non-clinicians can be equally effective compared to guidance delivered by specialists and clinicians (Leung et al., 2022). Therefore, using trained psychology students as e-coaches provides a cost-effective and scalable treatment method. In addition, we believe that the systematic screening process, personalized feedback, and a platform to communicate with an e-coach are promising approaches to allow students to recognize a problem and facilitate treatment seeking behaviors (Czyz et al., 2013).

The current study also assess the participants' satisfaction with treatment and e-coaches, program usability and treatment adherence. This will enable us to improve our program and the treatment experience further. Furthermore, the potential moderating variables will give us preliminary insights into who would benefit most from the treatment. Finally, the effectiveness of the intervention is tested in the same setting as it will be implemented. Moreover, while the participants receive compensation for completing all questionnaires, they do not receive any compensation for completing the program. This allows us to examine the real-life efficacy, demand and appeal of *GetStarted*.

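### Satisfaction, usability, working alliance and adherence arise after randomization and depend on using the program, so they cannot be tested as moderators of the randomized 4-week effect

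*Protocol article*

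**What the plan says.** The Introduction makes moderators of effectiveness a secondary research question and lists them: "These will be socio-demographic characteristics of the participants, satisfaction with treatment and e-coach, system usability and treatment adherence". Their purpose follows: "This will be done to identify target groups that could benefit most from treatment". The Abstract gives a matching list, and the Discussion expects that "the potential moderating variables will give us preliminary insights into who would benefit most from the treatment".

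Section 2.9.3 sets the analysis. It states: "Descriptive statistics will also be used for data exploration on the outcomes of the CSQ-8, SUS, WAI-I and adherence". The next sentence is "Additionally, these outcomes will be tested as predictors and moderators or treatment outcome", so the variables it refers to are these four. The tool is also fixed: "The moderation analyses will be conducted using PROCESS macro for SPSS version 3.4".

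Table 1 marks the CSQ-8, SUS-10 and WAI-I at T2 and T4 only, and its note defines the time points: "T2: 4 weeks post baseline – intervention group; T3: 4 weeks post baseline – waitlist group; T4: 8 weeks post baseline – waitlist group". Section 2.7.3 defines adherence as the percentage of main modules completed by post-test. Section 2.6 gives the waitlist arm no program for the first 4 weeks.

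Socio-demographics are collected at T0. The Abstract and Introduction call them moderators. Section 2.7.3 opens by giving socio-demographic and program variables a joint role as covariates and moderators, but its paragraph on socio-demographics mentions only covariates. Section 2.9.3 assigns them descriptive statistics and no test.

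**The concern.** Effectiveness in this trial means GetStarted against waitlist at 4 weeks. A moderator of that contrast must take meaningful values in both arms and must not itself result from treatment. Satisfaction with a program, its usability, the alliance with a coach and the number of modules completed meet neither condition.

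At stake is the answer to a stated secondary question. Ratings given at the same assessment as the IPS may reflect improvement as easily as they explain it. If their association with outcome is reported as moderation, correlates of doing well will be read as effect modification. Nor can a rating that exists only after treatment define a target group beforehand.

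**Working it through.** **Sample size, for reference.** The article gives no figure for the moderator analysis. Its main calculation (section 2.8) uses d = 0.50, two-sided alpha 0.05 and power 0.80. By the normal approximation, n per arm = 2 × ((1.960 + 0.842)/0.50)² = 62.8, so 63. With 28% dropout, 63/0.72 = 87.5, so 88 per arm and 176 in total. The stated figures reproduce, and 63 per arm is used below as the evaluable number.

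**What each arm has at the randomized comparison.**

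| Variable | Intervention, T2 (4 weeks) | Waitlist, T3 (4 weeks) | Waitlist, T4 (8 weeks, after access) |
|---|---|---|---|
| CSQ-8, SUS-10, WAI-I | collected | not collected | collected |
| Adherence | 0 to 100% | 0 by design | after access |
| Socio-demographics | from T0 | from T0 | from T0 |

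**Identification.** Section 2.9.3 does not write out the PROCESS model. The standard form for moderation of an arm effect is

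Y = b0 + b1·arm + b2·M + b3·(arm × M) + error, with b3 the moderation term.

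- *Adherence.* M = 0 for every waitlist participant, so arm × M equals M for everyone. Two columns coincide. A constructed design matrix with 88 per arm has rank 3 for 4 coefficients, so b2 and b3 cannot be separated.
- *CSQ-8, SUS-10, WAI-I.* M is missing for all waitlist participants at T3. Complete cases come from the intervention arm alone, where arm = 1 throughout, so the arm column equals the intercept and the product equals M. The rank is 2 of 4, and neither b1 nor b3 can be estimated.

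These results do not depend on sample size.

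**Possible rescues.** Imputing the scales at T3 would fill 100% of waitlist values with no observed waitlist data at that point, for ratings of something not yet used. Using T4 values takes measurements made after the waitlist arm had access, when no unexposed comparator remains; the Discussion itself concedes that long-term between-arm comparison is lost.

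**What a within-arm analysis would show.** A simulation of 63 treated participants gave everyone the same treatment effect, so true moderation is nil. Satisfaction was made to correlate with the post-test score (correlation assumed, 4,000 runs each):

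| Assumed correlation | Runs with p < 0.05 |
|---|---|
| 0.0 | 5% |
| 0.2 | 35% |
| 0.3 | 68% |
| 0.5 | 99% |

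A significant association is thus a common finding with no effect modification present.

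**What can be estimated.** For a binary baseline variable with share p in one category, in SD units, SE(b3) = √(2 × (1/(np) + 1/(n(1−p)))), where n is the number per arm.

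- n = 63, p = 0.5: SE = √(2 × (1/31.5 + 1/31.5)) = 0.356. The smallest interaction detectable with 80% power is 2.802 × 0.356 = 1.00 SD. Power for 0.5 SD is Φ(0.5/0.356 − 1.960) = 29%.
- n = 63, p = 0.7: SE = 0.389, smallest detectable interaction 1.09 SD, power 25%.
- n = 88, p = 0.5 (no dropout): SE = 0.302, smallest detectable interaction 0.84 SD, power 38%.

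The splits and the 0.5 SD interaction are assumptions; the article gives neither.

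**The case against.** The strongest reply is that little depends on this. Section 2.9.3 is headed exploratory, the Discussion promises only preliminary insight, and no primary estimate or sample size rests on it. That stands and limits the severity.

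A reader might infer that the aim of finding who benefits cannot be met at all. The article does not support this. The Abstract and Introduction name socio-demographic moderators, Table 1 measures them at T0, and section 2.9.2 plans separate analyses of depression and anxiety for students at or above 10 on the PHQ-9 or GAD-7 at baseline. The aim fails only through the four program variables. Equally, the descriptive-only treatment of socio-demographics in 2.9.3 is better read as inconsistent with the other sections than as a decision not to test them.

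The sentence at issue also says predictors. Associations with outcome among treated participants can be computed and reported as description, so that half stands.

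Some steps are inferred. The article neither specifies the PROCESS model nor says that multiple imputation extends to these variables. Section 2.9.1 places the waitlist post-test at t4 for the follow-up contrast, and on that reading waitlist adherence is not zero; but it then follows access and still gives no moderation of the randomized effect. The argument that improvement drives ratings applies less directly to adherence, which is a count of modules. None of this restores the missing interaction.

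**Conclusion.** The point holds for the four program variables. Moderation of the randomized 4-week effect by the CSQ-8, SUS-10, WAI-I or adherence is not identified, because the three scales are absent and adherence is constant at zero in the waitlist arm at that time. This follows from Table 1 and sections 2.6 and 2.7.3, given that moderation means an arm-by-variable interaction. The simulated rates rest on assumed correlations of 0.2 to 0.5 and only illustrate how easily a correlate could be mistaken for a moderator.

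Moderation by socio-demographics can be estimated, with power of about 25% to 38% for a 0.5 SD interaction under the assumptions shown, but the article must say consistently that it will be tested. Severity is moderate.

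**What to change.** 1. Remove the moderator label for satisfaction with treatment, satisfaction with the e-coach, usability and adherence in the Abstract, the Introduction and sections 2.7.3 and 2.9.3.
2. Analyse these four only among participants who had access to the program, as non-causal predictors or correlates of outcome, and do not impute them for waitlist participants before access.
3. State in 2.9.3 that the pre-randomization socio-demographic variables (age, gender, ethnicity, marital status, current psychotherapy or medication) are the ones tested for moderation, as exploratory arm-by-variable interactions in the 4-week model. Align the Abstract, Introduction and 2.7.3 with this.
4. Acknowledge the low power, for example about 29% for a 0.5 SD interaction with 63 per arm and an evenly split binary moderator, so that a null result is not read as a uniform effect.

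Interactions with baseline severity could be added but are optional. The cost is wording, settled before analysis, with no new data. The downside is a shorter list of claimed moderators.
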